#### Analysis of adherence data

Descriptive statistics will be used to examine exercise adherence and will be reported as numbers and percentages, or means and standard deviations, as appropriate. Exercise adherence will be measured by reporting the number of treatment sessions attended in each treatment group, and by reporting the following measures at each follow-up time-point:

• Self-reported exercise adherence (measured by agreement with the statement ‘I have been doing my exercises as often as I was advised’)

• Frequency and duration of physiotherapy exercise completed by the participant

• Change (from baseline) in level of physical activity (measured by PASE and, in a subsample of participants, accelerometry)

• Use of local exercise and physical activity facilities

#### Analysis of accelerometer data

Accelerometry data from the subsample of BEEP trial participants will be analysed using ActiGraph (version 6) accelerometer software. Prior to analysis, data will be cleaned by excluding time periods containing more than 60 minutes of zero count (where it is assumed the accelerometer is not being worn) and by including only those participants who have worn the accelerometer for at least 5 days for 10 hours or more. Sensitivity analyses will be conducted by changing the threshold to exclude minutes of zero count from 60, to 30 and 90 minutes respectively with the later threshold recommended for participants with knee pain
[72]. For each participant we will generate the following at each data collection point: number of valid minutes, counts per minute, proportion of time spent at each level of physical activity, using the cut-offs from Freedson et al
[73]. We will also calculate the proportion of participants meeting exercise/physical activity recommendations
[60].

Descriptive statistics will be given for the accelerometer variables at baseline and by treatment arm. Change (between baseline and each follow-up time point) in the average count per minute and in the proportion meeting the exercise recommendations will be analysed using analysis of covariance (ANCOVA) and logistic regression respectively with analyses adjusted for the covariates defined for the clinical effectiveness analysis and by treatment arm.

### Economic analysis

The economic evaluation will determine the cost-effectiveness of the two new physiotherapy-led exercise interventions to improve individual tailoring of, and adherence to, exercise in knee OA patients in primary care, in comparison to usual physiotherapy care. A cost-consequence analysis will initially be reported, describing all the important results relating to costs and consequences. Subsequently, an incremental cost-utility analysis will also be undertaken using patient responses to the EQ-5D-3 L questionnaire to calculate the incremental cost per additional quality-adjusted life year (QALY) gained.

#### Costs

Information on resource use and time off work will be collected from patient-completed questionnaires at 6 months, 18 months and 36 months. Health sector costs include primary and secondary care contacts, investigations, pain medications and contacts with other health care professionals. The cost of the interventions will also be determined taking into account any additional resource use required to deliver those interventions such as additional physiotherapy visits and telephone contacts and any additional equipment (e.g. pedometers) supplied to patients. The cost of the advice and information booklet will not be included as this will be given to all trial participants and will therefore be cancelled out in the cost analysis. Questions on patients’ personal expenditure will concentrate on private health care use and over-the-counter treatments. Due to the lack of nationally representative unit cost estimates for private health care, this care will be costed as the NHS equivalent in the base-case. Patient reported costs for over-the-counter treatments will be used.

Resource use will be multiplied by unit costs obtained from standard sources and health care providers including the British National Formulary (BNF), Unit Costs of Health and Social Care and NHS Reference costs
[74-76]. Productivity costs will be calculated using data collected on employment status at every time point and days off work due to knee pain. For those in paid employment, information on occupation, further details of typical work activities and the nature of their employment (full time or part time) will be requested. The average wage for each respondent will be identified using UK Standard Occupational Classification coding
[77] and annual earnings data for each job type
[78]. The analysis will use the human capital approach, and the self-reported days of absence will be multiplied by the respondent-specific wage rate.

The data for costs are likely to have a skewed distribution therefore the plan is to explore the nature of the distribution of costs. If the data are not normally distributed, then a non-parametric comparison of means, using bootstrapping, will be undertaken
[79].

#### Health economic outcomes

All patients will be asked to complete the EQ-5D-3 L questionnaire at baseline and at 3, 6, 9, 18 and 36 months in order that quality-adjusted life years (QALYs) over the time period can be calculated for each study participant, using the area under the curve method. If differences in baseline characteristics occur between intervention groups, for example in baseline EQ-5D-3 L score, the analysis will control for these baseline differences using regression-based adjustment
[80].

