#### Recruitment and follow-up

The number of participants identified and recruited using each recruitment method will be reported in a flow chart, along with the number of participants returning a questionnaire at each follow-up stage. The flow chart will include reasons for trial ineligibility and withdrawal (when available) and will be used to compare the recruitment success of each method to inform future trial recruitment.

The baseline characteristics of participants will be reported for the three recruitment methods, for the three treatment groups (to explore the effectiveness of randomisation) and for those with and without data at each follow-up time point (to explore any selective loss to follow-up). Any differences between treatment groups will be described by visual inspection rather than statistical testing.

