#### Primary and secondary trial analysis for clinical outcomes

The primary and secondary trial analysis will be conducted blind to intervention group by the statistician (EN) and an independent statistician will verify the analysis of the primary outcomes. The primary analysis will compare each of the Individually Tailored Exercise and Targeted Exercise Adherence interventions to usual physiotherapy care on an intention-to-treat basis, for the primary outcome at 6 months post-randomisation. Secondary analysis will include the analysis of the primary outcome at the secondary endpoints (3, 9, 18 and 36 months) and analysis of the secondary clinical effectiveness outcomes, as indicated in Table 
2, at all follow-up time points. Estimates of clinical effect will be derived using analysis of covariance (ANCOVA) for continuous outcome measures and logistic regression for dichotomous outcomes and will be presented as mean or percentage differences (as appropriate) with 95% confidence intervals after adjustment for baseline covariates defined *a priori* as:

• Baseline for the outcome of interest^a^

• Age

• Gender

• Duration of the knee problem

• Physiotherapy treatment centre (as was used in the randomisation algorithm)

A secondary analysis will also be completed to model the longitudinal trajectory of WOMAC pain and function over time (the primary outcome) and the PASE physical activity measure using generalized estimating equations. Model predictors will include the *a priori* covariates listed above (with the baseline for the outcome of interest modelled as a covariate rather than outcome as recommended in Peduzzi et al
[71]), time, treatment and a time*treatment interaction. A linear model will be fitted to the data (with time as a continuous measure) initially, however, if the trajectory over time is non-linear, quadratic or cubic terms will be explored. It will also be explored that conclusions do not differ if time is represented in the model as a categorical variable. All model estimates will be presented with 95% confidence intervals derived using robust standard errors.

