#### Cost-effectiveness analysis

The primary economic analysis will be conducted at 18 months, with additional analysis at 36 months. An intention-to-treat analysis will be undertaken. Multiple imputation techniques will be used to deal with missing EQ-5D-3 L scores and resource use data, ensuring that all eligible trial participants are included in the base case economic evaluation. All estimates will be presented as means with 95% confidence intervals.

The base case cost analysis will adopt a NHS and personal social services (PSS) perspective. A broader costing perspective will be considered in a sensitivity analysis, taking into account NHS/PSS costs, patients’ personal expenditure and costs associated with work loss. All costs and outcomes beyond 12 months will be discounted at the standard UK rate of 3.5%.

The estimation of cost-effectiveness within this trial will focus on the principles of dominance and extended dominance. Dominance is a straightforward concept; if an intervention is less effective and more costly than at least one of its comparators, it is not included for further consideration with regard to the estimation of cost-effectiveness. Extended dominance is applied in incremental cost-effectiveness analysis when an intervention is less effective and more costly than a linear combination of two other strategies; the purpose is to remove from consideration those strategies whose costs and benefits are improved by a mixed strategy of two other alternatives. The practical application of cost-effectiveness analysis is to compare an intervention with the next most effective strategy, therefore strategies are ordered in term of QALYs from least to greatest. Failure to remove all dominated or extendedly dominated strategies may lead to comparisons that are not with the next best alternative but with irrelevant alternatives.

The robustness of the results will be explored using sensitivity analysis. Deterministic sensitivity analysis will explore uncertainties in the methods employed to analyse the data, for example a complete case analysis as an alternative to using an imputed data set, any assumptions made in the analysis and the generalisability of the results to other settings.

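### QALYs are adjusted for baseline EQ-5D-3L only if a difference is judged to occur, with no trigger stated; adjusting in every case is more precise and leaves nothing to decide after the data are seen

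*Protocol article*

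**What the plan says.** Under Health economic outcomes, EQ-5D-3L is measured at six points: "All patients will be asked to complete the EQ-5D-3 L questionnaire at baseline and at 3, 6, 9, 18 and 36 months". QALYs are formed "using the area under the curve method". The adjustment rule follows: "If differences in baseline characteristics occur between intervention groups, for example in baseline" EQ-5D-3L, those differences are to be controlled for by regression. No size of difference, test or fixed covariate list is given, and baseline EQ-5D-3L appears only as an example. The Cost-effectiveness analysis section sets the horizon ("The primary economic analysis will be conducted at 18 months, with additional analysis at 36 months") and plans imputation and 5000 bootstrap replications, but it does not make the adjustment unconditional.

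The clinical analysis is fixed differently. Under Primary and secondary trial analysis for clinical outcomes, estimates are presented "with 95% confidence intervals after adjustment for baseline covariates defined" in advance, and the first item on the list is "Baseline for the outcome of interest". The only stated exception, in the endnote, is the responder criterion, which already uses baseline values. EQ-5D-3L is marked in Table 2 as a clinical effectiveness outcome, so its score at each follow-up falls under this unconditional rule.

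**The concern.** The same EQ-5D-3L responses are always baseline-adjusted when analysed as scores, but only conditionally when summed into a QALY. Yet the QALY depends on baseline in two ways: baseline is a term in the area under the curve, and it predicts every later term. Randomisation is stratified by clinic only, so baseline EQ-5D is not balanced by design.

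With no trigger, someone must decide whether a difference has occurred after seeing the baseline data. If the decision is not to adjust, any imbalance that was passed over stays in the incremental QALY, and precision already paid for by collecting baseline EQ-5D is not used. Strategies are ordered by QALYs before dominated ones are removed, so the point estimate and its uncertainty both feed the cost-effectiveness conclusion. The text also leaves open whether the decision is taken once or again in each bootstrap replication.

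**Working it through.** **The plan's own figure.** The article gives no figure for the QALY analysis. Its sample size reproduces: 2 × (1.96 + 0.8416)² / 0.35² = 128.1, so 129 per group and 387 in total; 387 / 0.8 = 484, rounded up to 500. That is about 167 per arm, used below because imputation is meant to keep all eligible participants in the base case.

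**Assumptions not in the documents.** EQ-5D SD 0.25 at every visit; correlation ρ between baseline and each follow-up of 0.3 to 0.6; correlation φ between follow-up visits of 0.5 to 0.7 and not below ρ; no discounting; no allowance for missing data.

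**Weights.** By the trapezium rule at 0, 3, 6, 9 and 18 months, the weights in years are 0.125, 0.25, 0.25, 0.5 and 0.375 (sum 1.5). The follow-up weights sum to 1.375.

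**Dependence on baseline.** The slope of QALY on baseline is β = 0.125 + 1.375ρ, that is 0.54 at ρ = 0.3 and 0.95 at ρ = 0.6. The SE of a chance baseline difference is 0.25 × √(2/167) = 0.0274. One such SE shifts an unadjusted QALY difference by 0.0274 × 0.54 = 0.015 to 0.0274 × 0.95 = 0.026. This applies only if that imbalance is left unadjusted.

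**Precision.** In units of SD², the QALY variance is V = 0.53125 + 0.34375ρ + 1.375φ. Then:
- unadjusted SE = 0.02736 × √V
- adjusted SE = 0.02736 × √(V − β²)
- SD under a conditional rule = 0.02736 × √(V − β² + Tβ²)

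Here T = 2Φ(k) − 1 − 2k·φₙ(k) is the share of the baseline difference's variance that stays unadjusted when the trigger is |z| > k, and φₙ is the standard normal density. The plan states no trigger, so two are used for illustration:
- Standardised difference above 0.1: k = 0.1/√(2/167) = 0.914, T = 0.159; about 36% of trials adjusted.
- p<0.05: k = 1.96, T = 0.721; 5% of trials adjusted.

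| ρ | φ | Unadjusted SE | Adjusted SE | SD, trigger 0.1 | SD, trigger p<0.05 |
|---|---|---|---|---|---|
| 0.3 | 0.5 | 0.0315 | 0.0278 | 0.0284 (+2%) | 0.0305 (+10%) |
| 0.3 | 0.6 | 0.0331 | 0.0296 | 0.0302 (+2%) | 0.0321 (+9%) |
| 0.3 | 0.7 | 0.0346 | 0.0313 | 0.0318 (+2%) | 0.0337 (+8%) |
| 0.6 | 0.6 | 0.0342 | 0.0222 | 0.0245 (+10%) | 0.0313 (+41%) |
| 0.6 | 0.7 | 0.0357 | 0.0244 | 0.0265 (+9%) | 0.0329 (+35%) |

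Percentages compare with always adjusting. Allowing ρ = 0.6 with φ = 0.5, where follow-up visits correlate less with each other than with baseline, would raise them to 13% and 50%.

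**Error rate.** In a simulation with no true difference (10,000 two-arm trials per scenario, ρ of 0.3, 0.5 and 0.7), always adjusting gave a type I error of about 0.05. The conditional rule gave 0.038, 0.030 and 0.020 with the 0.1 trigger, and 0.042, 0.040 and 0.030 with the p<0.05 trigger. A mechanically applied rule is therefore conservative: when it does not adjust, its interval is wider than it needs to be.

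**The case against.** A reader might infer that chance imbalance will drive the incremental QALY. The text does not support that. A noticed imbalance would be adjusted, only imbalance below the trigger remains, and over repeated trials this averages to zero.

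A reader might also set always adjusting against never adjusting and quote the whole fall in variance as the gain. Never adjusting is not the plan. The fair comparator is the conditional rule, whose loss is small if the trigger is sensitive and substantial only if it is strict.

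A third inference is that the trigger is judgement by eye, because Recruitment and follow-up says "Any differences between treatment groups will be described by visual inspection rather than statistical testing". That sentence governs how baseline tables are described. The economic section does not refer to it, so it cannot be taken as the trigger. What stands is that no trigger is given anywhere.

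Discretion is also partly exposed elsewhere. EQ-5D-3L scores at each visit are always analysed with baseline adjustment, and sensitivity analyses of the analytic methods are planned, so a reader could see a discrepancy. Neither fixes the QALY rule.

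Finally, some difference always occurs, so the condition could be read literally as always met. It then does no work and should be deleted; on any other reading it needs a threshold. Nor is this detail left to an analysis plan: the article states a rule, and the rule is poorly fixed.

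**Conclusion.** The point holds as a free improvement to the secondary economic objective. The conditional rule is less precise than always adjusting, and it leaves the choice of analysis open until the baseline data have been seen. The harm is avoidable variance, over-wide intervals and analyst discretion. It is not systematic bias, and a mechanically applied trigger does not inflate type I error.

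The loss lies between slight (about 2% in SD: low correlation, sensitive trigger) and about 41% (high correlation, p<0.05 trigger). These sizes rest on the assumed EQ-5D SD and correlations and on illustrative triggers. The direction does not, provided that baseline EQ-5D predicts the QALY, which it must in part because it is a term in it.

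**What to change.** Replace the conditional sentence with: *Incremental QALYs will in all cases be estimated by regression on treatment arm adjusted for baseline EQ-5D-3L.* Apply this in the base case and in the bootstrap replications, and report the unadjusted result as a sensitivity analysis. Adding the covariates already fixed for the clinical outcomes (age, gender, duration of the knee problem, treatment centre) is optional; the argument here does not depend on it.

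The cost is one sentence and one extra model term. Baseline EQ-5D-3L is already collected before randomisation, so no new data or participants are needed.

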#### Cost-effectiveness analysis

The primary economic analysis will be conducted at 18 months, with additional analysis at 36 months. An intention-to-treat analysis will be undertaken. Multiple imputation techniques will be used to deal with missing EQ-5D-3 L scores and resource use data, ensuring that all eligible trial participants are included in the base case economic evaluation. All estimates will be presented as means with 95% confidence intervals.

The base case cost analysis will adopt a NHS and personal social services (PSS) perspective. A broader costing perspective will be considered in a sensitivity analysis, taking into account NHS/PSS costs, patients’ personal expenditure and costs associated with work loss. All costs and outcomes beyond 12 months will be discounted at the standard UK rate of 3.5%.

The estimation of cost-effectiveness within this trial will focus on the principles of dominance and extended dominance. Dominance is a straightforward concept; if an intervention is less effective and more costly than at least one of its comparators, it is not included for further consideration with regard to the estimation of cost-effectiveness. Extended dominance is applied in incremental cost-effectiveness analysis when an intervention is less effective and more costly than a linear combination of two other strategies; the purpose is to remove from consideration those strategies whose costs and benefits are improved by a mixed strategy of two other alternatives. The practical application of cost-effectiveness analysis is to compare an intervention with the next most effective strategy, therefore strategies are ordered in term of QALYs from least to greatest. Failure to remove all dominated or extendedly dominated strategies may lead to comparisons that are not with the next best alternative but with irrelevant alternatives.

The robustness of the results will be explored using sensitivity analysis. Deterministic sensitivity analysis will explore uncertainties in the methods employed to analyse the data, for example a complete case analysis as an alternative to using an imputed data set, any assumptions made in the analysis and the generalisability of the results to other settings.

Probabilistic sensitivity analysis (PSA) will explore the uncertainty in the trial based data itself. Bootstrapping will be undertaken using STATA to produce 5000 bootstrap replications of cost-QALY difference pairs. These will be plotted on a cost-effectiveness plane to illustrate the uncertainty in the confidence to be placed on the results of the economic analysis. This will be further explored by estimating cost-effectiveness acceptability curves (CEACs)
[81]. These plot the probability that the intervention is cost-effective against threshold values for cost-effectiveness.

Finally, if one or more of the interventions demonstrates effectiveness for the full duration of the trial, the longer-term costs and benefits associated with that intervention will be explored using decision modelling approaches to extrapolate beyond the trial follow-up.

### Qualitative analyses

Data collection and analysis will be carried out iteratively so that emerging themes in the analysis can be explored in depth in the subsequent interviews. Earlier interviews (at the end of physiotherapy treatment completion) with individual participants will be analysed and inform the interview content of the interviews at the longer-term follow-ups. Sampling will continue until no new themes emerge.

We will use an emergent and layered approach to analysis
[82] that will allow for both induction and deduction. First, using the principles of constant comparison
[83], we will open code all transcripts. This will enable patient experiences of the interventions, general views on exercise and barriers and facilitators to exercise to be explored. A researcher will code the transcribed data, with a sample of interviews being independently coded by other members of the research team to ensure transparency and agree emergent themes at successive stages of the data collection and analysis. Second, we will apply a more deductive approach by re-reading transcripts and allocating data to predetermined codes of individualisation, supervision and progression (three core intervention constructs). Third, a focused within-case and cross-case longitudinal analysis will be performed by asking descriptive and interpretative questions of the data
[84]. Descriptive questions will investigate what has changed in terms of participants’ knee condition, adherence to the prescribed exercise programme or general physical activity levels, and the key influences on these changes. This will enable an overall understanding of what is different from the first interviews (post intervention) to the second (12 to 18 months after the end of the BEEP trial intervention) and potential reasons for any changes. Interpretive questions will then investigate, for example, which changes interrelate and how these might relate to existing theories of exercise adherence. Data summary frameworks
[82,84] will facilitate identifying patterns of change across time. Qualitative data analysis will be undertaken separate to the quantitative data analysis in the first instance to facilitate an interpretative approach and not constrain the analysis by quantitative variables or findings.

